### Participants

Private GPs, registered with the PMC and the SHCC, are deemed eligible to participate in the study. GPs outside Karachi, those working in welfare clinics, dentists, consultants and unqualified healthcare providers, are excluded from the study.

### Sample size

For this study, a list of 1695 GPs, obtained from the SHCC, has been considered a sample universe. From it, 419 GPs have been sampled using a systematic sampling technique. In our literature review, we identify no relevant surveys of private GPs in Pakistan, so we use data from two studies on medical students and trainee doctors, to calculate the sample size for our study. One survey of medical students shows that 81% favoured pharmaceutical sponsorship of events at medical colleges^27^ and the other study on trainee doctors in public hospitals indicates that 57% did not know any code of medical ethics.^28^ We estimate that 80% of private GPs in our sample will be classified as ‘supporting pharmaceutical incentivisation’ and assume that our intervention shifts this to 65%, in line with changes observed in the few interventional studies addressing COI in medical professionals.^29 30^ Using these assumptions, a sample size of between 130 and 135 per group gives a power of 80% to detect a difference owing to the intervention. As indicated in figure 2, the sample of 419 GPs was extracted in three steps. First, the entire list is screened to exclude 510 healthcare providers who do not meet our eligibility criteria. Second, information validation is performed by calling the remaining 1185 healthcare providers to verify important information such as clinic addresses, registration status, level of education and whether they are active/inactive in medical practice, further leading to the exclusion of 764 names. As part of a baseline survey on GPs’ knowledge and attitudes about ethics in medical practice, three GPs have been further excluded from the sample who refuse to participate in the study.

**Figure 2 F2:**
[figure not shown]
Flow chart of the sampling and randomisation process. GP, general practitioner; SHCC, Sindh Healthcare Commission.

### Randomisation

A total of 419 GPs, who completed the baseline survey and consented to attend the seminars, have been assigned to control and intervention groups, using a simple randomisation technique. Each GP in the list has been first assigned a unique identification number, following the sorting of the list with respect to six districts in Karachi, namely, East, West, Central, South, Korangi and Malir. Each GP has then been assigned a random number using the excel spreadsheet. Third, within each district, GPs are assigned to control and intervention groups by sorting the list. The intervention and control groups comprise of 210 and 209 GPs, of which, 135 and 132 GPs have attended the seminars. To prevent bias, we have collaborated with a statistician outside the research team to perform the randomisation process. Participants and data collectors are blinded in relation to GPs’ allocation to control and intervention groups.

### Data collection

To measure the impact of the intervention, our data collection is underway, and we anticipate completing it in September/October 2022. We adopt a multimethod approach to collect data on GPs’ knowledge, attitudes and practices in relation to COI linked with pharmaceutical incentivisation. Preintervention and postintervention surveys will be used to assess a change in GPs' knowledge of professional medical ethics and attitudes about engaging in pharmaceutical incentivisation. To collect information about their practices with respect to taking incentives for prescribing, a novel SPSR method will be used, in which trained field researchers will visit the GP clinics as pharmaceutical marketers to assess GPs’ reactions to pharmaceutical incentivisation offers. The SPSRs will recite a script (prepared by the research team) to introduce themselves and the imaginary pharmaceutical company and will market antibiotics commonly prescribed. In this process, the SPSRs make a clear incentivisation offer to GPs for prescribing the medicines and assess whether GPs accept/reject the offer. Since the SPSRs will be representing new pharmaceutical companies and there will be less familiarity between them and GPs, it is anticipated that there can be GPs’ responses, difficult to classify in terms of acceptance or rejection. Therefore, situations in which GPs ignore the SPSR offers or ask them to come back later will be classified as ‘undetermined’. The SPSRs will complete an electronic questionnaire after each GP visit to record information such as GPs’ demographic and clinical characteristics, and their responses to the incentivisation offer. To ensure the data quality, the research team will put several measures in place: recruiting field supervisors who will accompany the SPSRs to GP clinics and ensure the SPSRs’ responses in the questionnaire reflect the interactions with GPs, WhatsApp voice notes to the research team to summarise the interactions and monitoring the SPSR data considering the voice notes as a reference. The questionnaire will be analysed by research team members (also blinded to the allocation of GPs), who will assign a binary outcome for each GP such as ‘refused incentives immediately’, ‘refused incentives after being offered’, ‘asked for and accepted an incentive’, ‘offered and accepted an incentive’, ‘undetermined/undecided’. To prevent the SPSR assessment from being discovered as a simulation that not only can risk the intervention assessment but the SPSRs, in terms of their physical safety, each GP is paid a maximum of two visits. It is also important to note that the SPSRs are blinded to the allocation of GPs.

GPs have been made aware, through the consent procedure (online supplemental file 1) in the baseline survey, that their behaviour will be assessed covertly at some stage over 6 months but will not know details of the assessment to avoid the Hawthorne effect. We considered this novel SPSR approach to be superior to a revealed preference approach (eg, based on medical records) because records of prescribing by private physicians usually do not exist or are of poor quality in Pakistan, and to a stated preference design as it would rely on honest reporting of behaviour that is highlighted as unethical in the COI presentation.

10.1136/bmjopen-2022-067233.supp1Supplementary data

Finally, to explain the undecided/undetermined SPSR assessment outcomes, we will conduct 20–25 qualitative interviews with GPs and get information on the reasons why some GPs ignore talking to PSRs, asking them to come back later, and what it means when a GPs uses terms like ‘I am saturated/packed/engaged’.

### Data analysis

The primary outcome will be assessed by comparing the proportion of GPs classified as ‘yes’ to accepting an unethical benefit (according to the regulator’s guidelines) for prescribing the SPSR’s antibiotic between the control and intervention groups. The proportions will be compared using a two-proportion z-test. Secondary outcomes, such as knowledge and attitude shifts, will be assessed by comparing mean scores in survey responses of control and intervention groups using unpaired t-test and proportions scores in survey responses using the z-test.

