**Methods and analysis:**

This study is a randomised controlled trial to assess the impact of a multifaceted intervention on GPs’ medical practice. The study sample consists of 419 registered GPs who own/work in private clinics and will be randomly assigned to intervention and control groups. The intervention group GPs will be exposed to emotive and educational seminars on medical ethics, whereas control group GPs will be given seminars on general medical topics. The primary outcome measure will be GPs’ prescribing practices, whereas the secondary outcome measures will be their knowledge and attitudes regarding COI that arises from pharmaceutical incentivisation. In addition to a novel standardised pharmaceutical representatives (SPSR) method, in which field researchers will simulate pharmaceutical marketing with GPs, presurvey and postsurvey, and qualitative interviewing will be performed to collect data on GPs’ knowledge, attitudes and practices in relation to COI linked with pharmaceutical incentives. Univariate and multivariate statistical analyses will be performed to measure a change in GPs’ knowledge, attitudes and practices, while qualitative analysis will add to our understanding of the quantitative SPSR data.

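### Allocation was made within six districts but is called simple, and the primary z-test ignores district: a valid but slightly conservative test, costing little power unless districts differ widely

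*Protocol article*

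**What the plan says.** The Randomisation section says that the 419 GPs "have been assigned to control and intervention groups, using a simple randomisation technique". Its description of the steps is different. Identification numbers were given "following the sorting of the list with respect to six districts in Karachi, namely, East, West, Central, South, Korangi and Malir", each GP then received a random number, and finally: "Third, within each district, GPs are assigned to control and intervention groups by sorting the list". The result is reported as follows: "The intervention and control groups comprise of 210 and 209 GPs, of which, 135 and 132 GPs have attended the seminars".

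For the primary outcome, the Data analysis section compares the proportion of GPs in each arm who accept an unethical benefit, and names the test: "The proportions will be compared using a two-proportion z-test". District does not appear there. The Sample size section supplies the planning rates: "We estimate that 80% of private GPs in our sample will be classified as" supporting incentivisation, and the authors "assume that our intervention shifts this to 65" per cent.

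**The concern.** Two statements do not fit together. Ordering GPs by random number and assigning them within each district is stratified allocation. Simple randomisation would take no account of district. A reader who relies on the label will misunderstand how the arms were formed.

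The label also bears on the test. Splitting each district about evenly removes chance imbalance in district between the arms, so the difference in proportions varies less from trial to trial than it would between two unrestricted samples. The ordinary two-proportion z-test does not know this. It keeps the between-district variation in its standard error. When districts differ in acceptance, the interval is wider than it need be and the test rejects too rarely. What is at stake is precision and some power, on the one comparison the trial was sized for.

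**Working it through.** **Inputs from the article.** Six districts; 210 and 209 GPs randomised, of whom 135 and 132 attended; 80% versus 65%; 80% power with 130 to 135 per group.

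**Assumptions, because the article does not state them.** Two-sided 5% level; six districts of equal size; an even split within each district; the same absolute effect in every district; various spreads of district acceptance rates.

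**1. The plan's own sample size.** With unpooled variance, n per group = (1.96 + 0.8416)² × (0.80×0.20 + 0.65×0.35) / 0.15² = 7.849 × 0.3875 / 0.0225 = 135.2. The pooled-variance formula gives 138. Power by the pooled formula is 79.1% at 135 per group and 77.6% at 130. The stated range is therefore reproduced closely, with its lower end slightly optimistic. At 209 and 210 per group, power is 93.3%.

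**2. Why the standard error is too large.** Let p be the overall rate, s the standard deviation (SD) of the district rates and N the number per arm. With no treatment effect:
- variance assumed by the z-test: 2p(1−p)/N
- variance under an even within-district split: 2[p(1−p) − s²]/N
- ratio of standard errors: √{p(1−p) / [p(1−p) − s²]}

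At p = 0.80, p(1−p) = 0.16:

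| District SD | Ratio | Standard error too large by |
|---|---|---|
| 0 | 1 | 0% |
| 5 points | √(0.16/0.1575) = 1.008 | 0.8% |
| 10 points | √(0.16/0.15) = 1.033 | 3.3% |
| 13 points | √(0.16/0.1431) = 1.057 | 5.7% |

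Simulation at 132 per arm gave 0.6%, 2.7% and 5.6% for the last three rows, with actual type I error of 4.9%, 4.4% and 3.9%.

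**3. Power at the planned 15-point effect.** The unstratified z-test was compared with a district-stratified Cochran-Mantel-Haenszel (CMH) test in 200,000 simulated trials per case. Control rates were evenly spaced over the range shown. The two sizes are 22 per arm per district (132 per arm, near the number of attenders) and 35 per arm per district (210 per arm, near the number randomised).

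| Control rates by district | SD | Type I error, z-test | Power at 22 per arm per district, z-test → CMH | Power at 35, z-test → CMH |
|---|---|---|---|---|
| all 80% | 0 | 5.0% | 78.5% → 78.5% | 93.4% → 93.4% |
| 65–92% | 9 points | 4.4–4.5% | 77.8% → 78.9% | 93.2% → 93.7% |
| 30–90% | 21 points | 3.2–3.3% | 72.3% → 77.0% | 88.6% → 92.4% |
| 45–99% | 18 points | 3.2% | 74.0% → 79.4% | 91.5% → 94.0% |

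Type I error of the CMH test was 5.0% in every row. A separate run with the overall control rate held at 80% and a district SD of 10 points gave 79.0% → 80.5% at 132 per arm and 93.9% → 94.5% at 209. With an SD of 13 points (control rates 61% to 99%) it gave 79.4% → 82.0% and 94.3% → 95.3%.

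The loss is thus 0 with no district differences, 0.5 to 1.5 points for moderate spread, and about 2.5 to 5 points in the two widest scenarios. Those two also average 60% and 72%, below the planned 80%.

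**The case against.** The strongest reply is that nothing here threatens validity. An unadjusted comparison after stratified allocation keeps its type I error at or below 5%, and it errs towards finding no effect. That stands. A reader might infer from the mismatch that the z-test is wrong or that false positives rise; the direction is the opposite.

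It is also fair to say that the loss depends wholly on district differences, about which the article gives no figure. Its Discussion describes the GPs as having similar backgrounds, which gives no support to the widest scenarios. This stands too, and it limits the size of the point.

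Two stronger readings are tempting and should not be drawn:
- **That the trial is already short of power.** This needs a smaller effect than the planned 15 points. If GPs who did not attend were unaffected, the effect over all randomised GPs would be 15 × 135/210 = 9.6 points, but the article makes no such assumption. For the planned effect, power with everyone randomised is about 93%.
- **That the adjusted analysis has been dropped.** The abstract says "Univariate and multivariate statistical analyses will be performed to measure a change" and the Data analysis section names no model. Covariates and model details are commonly left to a fuller protocol or analysis plan, which is not shown, so their absence from the article is no defect.

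The named primary test is different. It is stated, not left open, and it does not use the strata that were used in allocation.

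**Conclusion.** The mismatch is on the page: allocation within districts is labelled simple, and the primary test takes no account of district. The consequence is a loss of efficiency, and it is conditional. Under the assumptions of equal districts, an even split and a common 15-point effect, the z-test gives up nothing when districts are alike, about 0.5 to 1.5 points of power for moderate spread with type I error near 4.4%, and about 2.5 to 5 points only for extreme spread. The mismatch and the direction of its effect are certain. The size is not, because it rests on district rates that the article does not give. If only the 267 attenders were analysed, within-district balance would no longer be guaranteed by design, which is a further reason to use district in the analysis. This is a labelling correction and a free improvement in the primary analysis.

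**What to change.** 1. In the Randomisation section, describe the allocation as stratified by district, with assignment by random-number order within each of the six districts.
2. In the Data analysis section, make the primary comparison district-stratified: a Mantel-Haenszel risk difference with 95% confidence interval and a CMH test, or an equivalent district-adjusted model.
3. Keep the unadjusted two-proportion z-test as a sensitivity analysis.

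The cost is a sentence or two. District is already known for every GP, and the stratified test loses nothing when districts are alike (78.5% against 78.5%, and 93.4% against 93.4%, above). The article reports data collection as still under way, so on its timetable the change could be written down before the arms are compared.

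### The primary SPSR outcome is analysed with an unadjusted two-proportion z-test that ignores allocation district and the complete pre-randomisation survey, which is valid but may give up some precision at no saving

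*Protocol article*

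**What the plan says.** The Data analysis section compares the proportion of GPs who accept an unethical benefit between arms and gives one method for it: "The proportions will be compared using a two-proportion z-test". It names no covariate, stratum or model. For the secondary outcomes it lists unpaired t-tests and z-tests.

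The Methods and analysis paragraph of the abstract is broader: "Univariate and multivariate statistical analyses will be performed to measure a change in GPs’ knowledge, attitudes and practices". Practices are the primary outcome.

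Two kinds of pre-allocation information exist:

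- **Survey.** The Sample size section refers to "As part of a baseline survey on GPs’ knowledge and attitudes about ethics in medical practice", and the Randomisation section says "A total of 419 GPs, who completed the baseline survey and consented to attend the seminars, have been assigned to control and intervention groups". The survey is therefore complete for every randomised GP and precedes assignment. The Data collection section adds that the surveys cover attitudes to engaging with pharmaceutical incentives.
- **District.** The Randomisation section says the list was sorted by six Karachi districts and that GPs were assigned to arms within each district.

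**The concern.** The SPSR response has no baseline measurement of its own, so any precision gained from baseline data must come from other variables. The survey scores are plausible candidates, since they concern knowledge of ethics and attitude to the kind of offer the SPSR makes. District is a candidate because the allocation used it. An unadjusted test leaves whatever variation these explain in the error term.

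At stake is the width of the primary interval and, to a lesser degree, power. There is also a question of clarity. The abstract announces a multivariate analysis of practices, and the section that fixes the methods does not say what it is or how it stands to the z-test. The SPSRs also record GP characteristics at the post-intervention visit, so a model whose covariates are not named could draw on data collected after randomisation.

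**Working it through.** **Inputs from the protocol article.** Sample size section: "We estimate that 80% of private GPs in our sample will be classified as" supporting incentivisation, with a shift to 65% under the intervention; 80% power; 130 to 135 per group. Randomisation section: 210 intervention and 209 control GPs, of whom 135 and 132 attended the seminars.

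**Assumptions.** Two-sided 5% significance, which is not stated; one-sided 5% would need only 107 to 109 per group without continuity correction. R² is the share of outcome variance explained by the baseline covariates. It is not in the document and is taken over 0 to 0.10. The article does not say whether all randomised GPs or only attenders are analysed, so both are shown.

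**Step 1: the plan's own figure.** Unpooled formula:

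n = (1.96 + 0.8416)² × (0.80×0.20 + 0.65×0.35) / 0.15² = 7.849 × 0.3875 / 0.0225 = 135.2 per group.

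The pooled version gives 138. Unpooled power is 78.4% at 130 per group and 79.9% at 135. The stated range is thus reproduced, to within 2 power points, by an unadjusted comparison of two proportions.

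**Step 2: unadjusted power of the z-test at the actual numbers.** Power = Φ[(0.15 − 1.96·SE₀)/SE₁], where SE₀ uses the pooled proportion and SE₁ the separate ones.

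- 132/135: pooled proportion 193.35/267 = 0.724; SE₀ = 0.0547; SE₁ = 0.0538; (0.15 − 0.1072)/0.0538 = 0.795; power 78.7%.
- 209/210: pooled proportion 303.7/419 = 0.725; SE₀ = 0.0436; SE₁ = 0.0430; (0.15 − 0.0855)/0.0430 = 1.50; power 93.3%.

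**Step 3: adjusted.** Both standard errors are multiplied by √(1 − R²). At R² = 0.10 the factor is √0.90 = 0.949. For 132/135 this gives (0.15 − 1.96×0.0519)/0.0511 = 0.945, so power is 82.8%.

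| R² | SE factor | Power, 132/135 | Power, 209/210 | 95% CI half-width, 132/135 (points) |
|---|---|---|---|---|
| 0 | 1.000 | 78.7% | 93.3% | 10.6 |
| 0.02 | 0.990 | 79.5% | 93.8% | 10.4 |
| 0.05 | 0.975 | 80.7% | 94.4% | 10.3 |
| 0.10 | 0.949 | 82.8% | 95.4% | 10.0 |

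Over this range the gain is 0 to 82.8 − 78.7 = 4.1 points with 132/135 and 0 to 95.4 − 93.3 = 2.1 points with 209/210. The interval narrows by 0 to 5% in both cases.

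**Step 4: simulation check.** In 4,000 runs at 132/135, a standardised risk difference from a logistic model with one baseline covariate was set against the z-test.

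- Useless covariate: variance ratio (adjusted/unadjusted) 1.00; power 78.3% adjusted against 78.2% unadjusted.
- R² about 0.03: variance ratio 0.97; power 79.7% against 78.2%.
- R² about 0.07: variance ratio 0.93; power 83.1% against 78.8%.
- No true effect: rejection rate 5.1 to 5.3% for both tests.

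The gain at R² of about 0.07 (4.3 points) is somewhat above the formula, whose gains are 2.0 points at R² = 0.05 and 4.1 at 0.10. Monte Carlo error on each simulated power is √(0.8×0.2/4000), about 0.6 points. The variance ratios agree with 1 − R².

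**The case against.** The strongest reply is that nothing here is wrong. The z-test is a valid comparison in a randomised trial, it holds its error rate, and it is the analysis on which the sample size rests. Chance imbalance in baseline attitude is not bias, because the test's standard error already allows for it. All of this stands.

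A reader might infer that the trial certainly loses precision. The document does not support that. It gives no correlation, and its own text suggests the link may be weak: the Introduction cites a know-do gap, and the Data collection section rejects a stated-preference design because it would depend on honest self-report. If the scores do not predict behaviour, the gain is zero.

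A reader might also infer two rival headline results. That goes too far. The Data analysis section ties one named test to the primary outcome, and the abstract does not call the multivariate analysis primary. A z-test with a supporting model would satisfy both.

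Nor is it a fault that a condensed article leaves model details to an analysis plan that is not shown. What the article does fix is the primary test, and that test uses none of the available baseline information.

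Finally, data collection is already underway, so replacing the published primary test is a real change. That also stands and belongs in the cost.

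**Conclusion.** The point holds as a modest improvement. The primary test is sound but uses neither the allocation district nor the complete pre-randomisation survey, and the Data analysis section does not identify the multivariate analysis of practices that the abstract announces.

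The size depends on an R² that the document does not give and on which GPs are analysed. With R² between 0 and 0.10, an assumed 5% two-sided test and the plan's 80% versus 65%, the gain is 0 to about 4 power points if only the 132/135 attenders count, and 0 to about 2 if all 209/210 do. A claim that adjustment is needed for validity, or that power is seriously short without it, would not be supported. The case for adjusting is that the possible gain comes from data already in hand, and that the simulation found no cost in error rate or power when the covariate was useless.

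**What to change.** Before allocation is revealed, amend the Data analysis section to say that:

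- the primary estimate is the difference in proportions between arms with a 95% confidence interval, standardised over the analysed GPs from a logistic model with arm, district, and the baseline attitude and knowledge scores;
- the scores come from the pre-randomisation survey, not from the characteristics that SPSRs record at the visit, and how each score is formed is defined in advance;
- the two-proportion z-test is kept as the unadjusted sensitivity analysis;
- this model is the multivariate analysis of practices meant in the abstract.

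The cost is a few sentences and a few lines of code, with no new data and no more GPs. The downsides are a headline test slightly less simple than a z-test, and a change to the published primary analysis while data collection is underway. That change should be dated, documented and made blind to allocation.

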### Outcome measures

The primary outcome measure of the study is the number of GPs who refuse to take unethical pharmaceutical incentives from the standardised PSRs (SPSRs). The secondary outcomes include GP’s change in knowledge and attitudes about professional ethics in medical practice.

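### Knowledge and attitude outcomes are tested without baseline adjustment, and the plan does not say whether follow-up or change scores are compared; either reading gives up precision that is free to recover

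*Protocol article*

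**What the plan says.** The Outcome measures section defines the secondary outcomes as "change in knowledge and attitudes about professional ethics in medical practice". The Data collection section gives the surveys the same purpose: "Preintervention and postintervention surveys will be used to assess a change in" knowledge and attitudes.

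The Data analysis section then fixes the tests. It introduces them with "Secondary outcomes, such as knowledge and attitude shifts, will be assessed by comparing mean scores in survey responses". The test for means is given as "comparing mean scores in survey responses of control and intervention groups using unpaired t-test", and the test for proportions as "proportions scores in survey responses using the z-test". It names no covariate, and it does not say whether the score is the follow-up value or the difference from baseline.

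The baseline measurement exists for every randomised GP. The Randomisation section begins: "A total of 419 GPs, who completed the baseline survey and consented to attend the seminars". The Sample size section gives the subject of that survey when it reports a late exclusion: "knowledge and attitudes about ethics in medical practice, three GPs have been further excluded". The Randomisation section also says that GPs were allocated to arms within each of six districts.

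One further statement bears on the point. The abstract, under Methods and analysis, says: "Univariate and multivariate statistical analyses will be performed to measure a change in" knowledge, attitudes and practices. No model or covariate is given there, and the Data analysis section describes none.

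**The concern.** The outcome is defined as a change, and a pre-randomisation measurement of the same constructs is held for everyone randomised. Yet the only tests named for it have no place for a baseline covariate. A GP's earlier score on knowledge or attitudes usually predicts the later one, so an analysis that conditions on it removes between-GP variation that an unadjusted test leaves in the standard error.

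The wording also matters. A t-test on follow-up scores and a t-test on change scores have different standard errors, and which is larger depends on the correlation between the two surveys. As written, two analysts could follow the section faithfully and report different intervals. What is at stake is the width of the intervals for the secondary outcomes, and certainty about which analysis was intended.

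**Working it through.** **The plan's own figure.** The article gives no precision or power calculation for the knowledge and attitude scores. Its only calculation is for a binary outcome, 80% against 65%, with 130 to 135 per group at 80% power. Assuming two-sided alpha 0.05 and unpooled variance, n = (1.960 + 0.842)² × (0.80 × 0.20 + 0.65 × 0.35) / 0.15² = 135.2 per group. That reproduces the upper end of the stated range, but it does not bear on this point.

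**Inputs.**
- Randomised: 210 and 209 (Randomisation section).
- Attended the seminars: 135 and 132 (same section), used as a smaller-sample case. The number with a follow-up survey is not stated.
- SD of the scores: not stated, so results are in SD units.
- Correlation r between baseline and follow-up score: not stated, taken as 0.3, 0.5 and 0.7.
- Also assumed: equal SD at both surveys, the same r in both arms, and large-sample variances.

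**Formulas.** Variance of the between-arm difference, relative to a follow-up-only t-test:
- follow-up only: 1
- change score: 2(1 − r)
- ANCOVA: 1 − r²

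ANCOVA is never worse. Against follow-up only, 1 − r² ≤ 1. Against change scores, 2(1 − r) − (1 − r²) = (1 − r)² ≥ 0. The change-score test is less precise than ignoring baseline whenever 2(1 − r) > 1, that is, r < 0.5.

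**Interval width, ANCOVA against each reading.** The width ratio is √(1 − r²) against follow-up only. Against change scores it is √[(1 − r²) / (2(1 − r))] = √[(1 + r)/2].

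| r | ANCOVA / follow-up only | narrower by | ANCOVA / change score | narrower by |
|---|---|---|---|---|
| 0.3 | √0.91 = 0.954 | 5% | √0.65 = 0.806 | 19% |
| 0.5 | √0.75 = 0.866 | 13% | √0.75 = 0.866 | 13% |
| 0.7 | √0.51 = 0.714 | 29% | √0.85 = 0.922 | 8% |

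**95% half-widths in SD units.** For follow-up only with 210 and 209: 1.96 × √(1/210 + 1/209) = 0.192. With 135 and 132: 1.96 × √(1/135 + 1/132) = 0.240. Multiplying by the square roots of the relative variances gives:

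| r | 210/209: follow-up | change | ANCOVA | 135/132: follow-up | change | ANCOVA |
|---|---|---|---|---|---|---|
| 0.3 | 0.192 | 0.227 | 0.183 | 0.240 | 0.284 | 0.229 |
| 0.5 | 0.192 | 0.192 | 0.166 | 0.240 | 0.240 | 0.208 |
| 0.7 | 0.192 | 0.148 | 0.137 | 0.240 | 0.186 | 0.171 |

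At r = 0.5 the variance falls by 25% against either reading, equivalent to 1/0.75 = 1.33 times as many GPs.

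These figures are for mean scores and adjust for baseline only. No gain was computed for the survey proportions or for adding district.

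**The case against.** A reader might infer that the baseline survey is discarded. The documents do not establish that. The analysis section speaks of shifts, the outcome is defined as change, and the two surveys exist to measure change. All of this fits an unpaired t-test on each GP's change score, which does use baseline. The statement that stands is narrower: neither reading adjusts for baseline, and the section does not say which reading is meant.

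A reader might also infer that a follow-up-only t-test misses the defined outcome, or that chance imbalance at baseline biases it. Neither follows. Baseline was measured before randomisation, so the arms have equal expected baseline means, and the difference in follow-up means has the same expectation as the difference in mean change. Chance imbalance is part of the sampling error that the t-test's standard error already covers.

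The strongest procedural objection is that the abstract promises multivariate analyses, and that an article may leave the model to a fuller protocol or SAP that is not shown. That is a fair reason not to call the adjusted model missing. It does not remove the point, because the article does fix tests for these particular outcomes, and they are unadjusted. If an adjusted model exists elsewhere, the article does not say that it takes precedence over the t-test and z-test.

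Finally, the gain depends on an unknown correlation. If r is 0.3 or lower, the gain over a follow-up-only t-test is about 5% or less. It also applies only to GPs who return a follow-up survey. Both limits stand.

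**Conclusion.** The point holds as one of efficiency and clarity. The tests named for the knowledge and attitude outcomes are valid under randomisation. For mean scores, though, they are less precise than ANCOVA under either reading, for any r strictly between 0 and 1. Over r from 0.3 to 0.7, the ANCOVA interval is 5% to 29% narrower than a follow-up-only interval and 19% to 8% narrower than a change-score interval.

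These sizes rest on assumed correlations, equal SDs at the two surveys and large-sample formulas. For the proportions, the lack of baseline adjustment is clear from the text but the gain is unquantified. The primary outcome is not affected, and no bias is alleged. The change is recommended because the baseline data are already in hand.

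**What to change.** - **Mean scores:** make the main secondary analysis a linear regression of the follow-up score on arm, the same baseline score and district. District belongs in the model because allocation was made within district. This also settles whether follow-up or change is analysed, since with baseline as a covariate the arm effect is the same for both.
- **Survey proportions:** use logistic regression on arm, baseline response and district, reported as a standardised risk difference so that the result stays on the scale of the two-proportion comparison.
- **Reporting:** show the unadjusted t-test and z-test results alongside, saying explicitly whether the t-test is on follow-up or change scores, and state how the abstract's multivariate analyses relate to these models.

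The cost is analysis wording only, with no new data, visits or GPs. The article describes data collection as still under way, so the wording can be settled before results are examined.
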